**FIGURE 3 epi470064-fig-0003:**
[figure not shown]
Data transfer flow of the 24/7 EEG SubQ solution using a 3rd‐party hosting service provider. Both the UNEEG EEG review services and the healthcare professionals have access to the data via a web browser.

Specialized third‐party contract research organization Clinigma (Copenhagen, Denmark) will conduct qualitative semi‐structured interviews with participants at baseline (between Visit 1 and Visit 2) and at exit (in the period of 14 days after their Visit 5). Timepoints are chosen to obtain participants' insights before implantation (baseline interview) and before explantation (exit interview). Clinigma will also conduct interviews with a nominated treating clinician from each of the sites.

All treating clinicians and investigators will undergo Good Clinical Practice (GCP) training.

### Seizure detection

3.2

Continuous EEG monitoring will generate substantial data; therefore, an automated solution is required. Automated algorithms for seizure detection in multichannel EEG (reviewed by Baumgartner et al.^29^) show seizure detection sensitivity 59%–96% (median 81.4%) and false detection rate 0.08–5.38 per hour (median 0.3 per hour). The EEG analysis software AI algorithm that will be utilized (implemented within UNEEG EpiSight Analyzer) was trained using EEGs from 490 people (Temple University) and optimized on 24/7 EEG SubQ data from 32 participants. A deep neural network based on ResNet and a feature pyramid structure was designed to recognize seizures. Using 24/7 EEG SubQ data from nine PWE,^30^ a mean sensitivity of 89% and mean false positive rate 5.5/24 h was achieved. Hence, our algorithm is comparable to other multichannel EEG detection algorithms.^29^

Data will be screened by experienced neurophysiology technicians to remove suspected false positives prior to treating clinician review. Treating clinicians will be provided with annotated EEG data and a report summarizing the previous week's EEG data at weekly intervals and will have access to the continuous EEG recordings at any time.

## OUTCOMES

4

The primary outcome measures of this study include: (A) Within participant correlation between seizure counts per month estimated from clinician review of annotated 24/7 EEG SubQ data (hybrid AI‐seizure detection algorithm and neurophysiology technician review) and ‘ground truth’ EEG seizure occurrences per month (derived from expert research team review of 24/7 EEG SubQ data); (B) Within participant correlation between seizure counts per month from participant reported seizure diary and ‘ground truth’; (C) Average difference between ‘correlation A’ and ‘correlation B’; (D) Average difference between the number of AI driven seizure detections and seizure counts estimated from rapid clinician review of annotated 24/7 EEG SubQ data (clinician inspection of data), across participants; and (E) Clinician rating of accuracy (compared to their own review) of annotated 24/7 EEG SubQ data.

A complete list of primary and secondary objectives with corresponding outcomes can be found in Table 1.

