### Sample size

2.4

We powered our study based on the primary outcome measure for diagnostic accuracy. We used data from an intracranial EEG study,^18^ which shows the correlation between the monthly number of seizure occurrences documented using participant self‐reported diary and the ground truth seizure occurrences per month, documented with the intracranial Neurovista device. The mean correlation across the group is 0.30 (SD 0.41). We seek to demonstrate a higher correlation between 24/7 EEG SubQ and the ground truth seizure occurrences. We chose a modestly higher correlation of 0.5 to power this study. At alpha 0.05, 33 participants would give 85% power to demonstrate an improvement in within‐participants correlation from 0.3 to 0.5 (calculated using G*Power).

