### Statistical analysis of primary outcome measures

4.1

The research team will review raw EEG data from 24/7 EEG SubQ to identify seizures as the ‘ground truth’. We will assess the improvement in accuracy of seizure documentation using AI‐driven algorithm with rapid expert review applied to 24/7 EEG SubQ data (‘24/7 EEG SubQ detected seizures’), compared to using self‐reported participant diary alone. We will estimate for each participant the Spearman correlation between monthly diary report and ground‐truth, and the Spearman correlation between monthly 24/7 EEG SubQ detected seizures and ground truth. We will test the hypothesis that, across the cohort, the correlation between 24/7 EEG SubQ detected seizures and ground truth is higher than between the diary and ground truth. We will also calculate for diary and 24/7 EEG SubQ detected seizures the sensitivity, specificity, false positive rate, positive predictive value, and negative predictive value, for seizure detection. We will report using Standards for the Reporting of Diagnostic accuracy studies (STARD) principles.^31^

Feasibility and acceptability will be assessed by the proportion of participants who continue in the study for >3 months of 24/7 EEG SubQ data collection.

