### Statistical analysis of secondary outcome measures

4.2

Clinical relevance, changes in the clinical management plan for the participant, degree of confidence level of investigators initiating a change in their participant's clinical management plan, based on the input from the EEG data recorded with 24/7 EEG SubQ Solution, will be assessed by questionnaires.

Participant's reaction to receiving feedback on EEG data recorded with 24/7 EEG SubQ will be captured using an average score on a 10‐point Likert scale (positive (10) to negative (1)).

Adherence, acceptability, and performance will be assessed by: (1) Proportion of total study time (wear time) during which 24/7 EEG SubQ data are collected; (2) Questionnaires; (3) Proportion of Device Deficiencies.

In order to assess quality of life we will assess change over time for average EQ‐5D‐5L scores at baseline, 2 months and 6 months, change over time for average Participant Weighted Quality of Life In Epilepsy (QOLIE‐31‐P) scores at baseline, 2‐months and 6 months, change over time for average Impact of epilepsy scores at baseline, 2‐months and 6 months, and change over time for average Perceived self‐mastery over epilepsy scores at baseline, 2‐months and 6 months.

Costs and health outcomes will be estimated over a lifetime time‐horizon in order to consider longer‐term health and economic implications. Results of analysis will be presented in terms of cost per quality‐adjusted life‐year (QALY) gained. Average Client Services Receipt Inventory (CSRI) scores will be assessed at 6 months.

In order to compare our cohort with similar controls without 24/7 EEG SubQ, we will utilize historical controls from a recently completed study,^32^ which included 198 participants in the Treatment As Usual arm with ≥10 seizures/year. These participants were recruited similarly and completed four outcome measures that we will use at baseline and 6 months and CSRI.

In addition to the above, adverse events will be recorded throughout the study.

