### Statistical analysis methods

4.3

The accuracy of the two groups, i.e., (1) AI‐driven algorithm with rapid expert review applied to 24/7 EEG SubQ data vs. ground truth and (2) self‐reported participant diary vs. ground truth, will be compared in two ways: a correlation‐based comparison and an agreement‐based comparison. For the correlation‐based comparison, we will first estimate Spearman correlation coefficients for both groups to evaluate their monotonic relationship with the ground truth. To compare these relations between the two groups, we will use a Wilcoxon signed‐rank test. For the agreement‐based comparison, we will use the Bland–Altman method to allow us to calculate the mean difference and the limits of agreement to determine if one group consistently over‐r underestimates the ground truth compared to the other group.^33^

Questionnaire‐based data (see Table 1) will be assessed using different methods. For categorical data collected at three different time points (start, 2 months, and 6 months), the Chi‐squared test will be used to assess whether there are significant changes in the distribution of responses over time. Likert scale's and the CSRI will be assessed with descriptive statistics (e.g., mean, median, and frequency distributions) to summarize participant responses. For comparing the quality‐of‐life questionnaires (e.g., EQ‐5D, QOLIE‐31‐P) between the study cohort and historical controls, the Mann–Whitney U test will be used. Differences will be considered significant at *p* < 0.05.

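### Correlation B sets unrestricted monthly diary counts against a ground truth that exists only while the device records, so unworn time lowers B but not A and biases their difference towards the device

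*Protocol article*

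**What the plan says.** Table 1 (section 3.1), Outcomes (section 4) and section 4.1 all define the primary comparison.

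- **Ground truth:** seizures found by the research team on review of the raw SubQ EEG (4.1). There is no second source.
- **Correlation A:** monthly counts from clinician review of annotated SubQ data, against that ground truth.
- **Correlation B:** "Within participant correlation between seizure counts per month from participant reported seizure diary and" the same ground truth. Section 4.1 repeats it: "We will estimate for each participant the Spearman correlation between monthly diary report and" ground truth. Table 1 adds that it runs across the 6 months of the study.
- **Outcome (C):** the average of A minus B. Section 4.3 tests it: "To compare these relations between the two groups, we will use a Wilcoxon" signed-rank test.
- **Further diary measures:** section 4.1 plans sensitivity, specificity, false positive rate and predictive values for diary and device. Section 4.3 plans a Bland-Altman comparison.
- **Wear:** section 4.2 and objective 6 of Table 1 make recording completeness an outcome: "Proportion of total study time (wear time) during which 24/7 EEG SubQ data are collected". No expected or minimum wear is given.

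Diary and EEG both start at Visit 3 (section 3), so the calendar windows agree. Only hours without recording separate the two sources. The article has no rule for diary entries made in those hours.

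**The concern.** A seizure that happens while the external unit is off, and that the participant enters correctly, has no EEG counterpart. It adds to the diary count but not to the ground truth, so a correct entry is scored as disagreement. The device cannot be penalised in the same way, because its count and the ground truth lose the same hours together. When wear differs between months, A's two counts rise and fall together and B's do not. Even constant wear below 100% lowers B, because chance decides which seizures fall in recorded time.

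At stake is what outcome (C) measures. It is meant to compare how well two sources document seizures. As worded, it also includes a penalty for non-wear that falls on the diary alone. The penalty is largest for accurate diary keepers, and the inclusion criteria require people who routinely keep a diary. Two secondary measures are also affected. True entries in unrecorded time become false positives, which lowers the diary's positive predictive value. They also move the diary's Bland-Altman mean difference upwards.

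**Working it through.** **1. The plan's own figure.** Section 2.4 states: "The mean correlation across the group is 0.30 (SD 0.41"), and "We chose a modestly higher correlation of 0.5 to power this study". The difference is 0.5 - 0.3 = 0.20, and d = 0.20/0.41 = 0.488. With n = 33, a one-sided 5% paired t test has 86.4% power, and the Wilcoxon test (efficiency 3/pi) has 84.9%. The stated 85% is therefore reproduced as a one-sided figure with 0.41 taken as the SD of the paired difference (two-sided: 77.6% and 75.5%). The mismatch does not alter this arithmetic. The yardstick it supplies is the design difference of 0.20.

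**2. Model.** For each participant and month:

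- all seizures N ~ Poisson(m), with m = 2, 5 or 10 (assumed);
- wear w ~ Uniform(lo, 1), with lo = 0.9 or 0.7 (assumed), independent of seizures;
- ground truth G ~ Binomial(N, w);
- device count ~ Binomial(G, s_E);
- diary entries inside recorded time, D_in ~ Binomial(G, s_D), and outside it, D_out ~ Binomial(N - G, s_D).

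A is the six-month Spearman correlation of the device count with G. B as worded uses D_in + D_out against G. B matched uses D_in against G. A one-sided 5% Wilcoxon test is applied to A minus B in 33 participants.

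**3. The document's own accuracy figures.** Section 1.1 cites 44%-56% of seizures unreported, so s_D is about 0.5. Section 3.2 cites 89% sensitivity for the algorithm, so s_E = 0.89.

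| Monthly wear | B matched | B as worded | Inflation of A minus B | Test favours device |
|---|---|---|---|---|
| 90-100% | 0.64 | 0.62 | 0.02 | 100% either way |
| 70-100% | 0.65 | 0.57 | 0.08 | 100% either way |

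Against 0.20, this is 0.02/0.20 = 10% to 0.08/0.20 = 40% of the design difference. A second model used overdispersed counts (gamma shape 3), 3 or 10 seizures a month, diary capture varying by month and some device false positives. It gives inflation of 0.03 at 90% mean wear, 0.06 at 80% and 0.09-0.10 at 70%.

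**4. No true difference.** Share of trials in which the test favours the device:

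| Capture, diary = device | Counts | Wear 90-100% | Wear 70-100% |
|---|---|---|---|
| 50% | Poisson | about 9% | about 29% |
| 90% | overdispersed (gamma shape 1) | about 20% | about 81% |
| 90% | Poisson | about 40% | about 98% |

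With diary entries limited to recorded time, rejection in the 90% Poisson setting is about 4-7%, close to nominal.

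**5. Limiting case.** With a perfect diary and a perfect device (second model's counts, wear varying by month), A stays at 1.00. B as worded falls to 0.94 at 90% mean wear, 0.88-0.89 at 80% and 0.77-0.78 at 60%. Matched, B is 1.00. At 100% wear there is no bias.

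**6. Other diary measures.** If mean wear is w, a share 1 - w of true entries falls outside recorded time: 20% at 80% wear, all counted as false positives. The Bland-Altman mean difference (diary minus ground truth) rises by s_D(1 - w)m. At s_D = 0.5, w = 0.8 and m = 10 that is 0.5 x 0.2 x 10 = 1.0 seizure a month: -3.0 (5 - 8) in place of -4.0 (4 - 8). Event-level sensitivity is unaffected: its denominator is ground-truth seizures, and an entry in unrecorded time cannot match any of them.

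**The case against.** **The article is condensed.** It never states that diary entries from unrecorded hours count. It gives monthly counts without a restriction, and a matching rule is the kind of detail a full protocol or SAP may hold. This stands in part: a reader might infer that the trial has decided on a whole-month comparison, and the text does not establish that. But the article defines B in three places, and each, followed as written, gives the mismatch.

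**The alarming figures need a very good diary.** A reader might infer that the primary test is nearly bound to favour the device wrongly, since false rejection reaches 98%. The documents do not support that. The figure needs a diary capturing 90% of seizures, Poisson counts and wear varying over 70-100%. The article itself cites about half of seizures unreported and a mean diary correlation of 0.30. On its own accuracy figures the test rejects with or without matching. This stands in full, and it confines the expected harm to the size of the estimate.

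**Matching changes the question.** The trial is about real-world documentation, and non-wear is a real shortcoming of the device. Restricting the diary to recorded hours takes that shortcoming out of the comparison. This is fair, and it is why the all-entries analysis should be kept. The current wording does not capture the shortcoming either: it charges non-wear to the diary.

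**Conclusion.** The bias follows from the endpoint as worded, and its direction is clear: wear below 100% lowers B, leaves A unaffected and moves outcome (C) towards the device. Its size is not known, because the documents give no wear figure. Under the article's own diary and device accuracy, A minus B is inflated by about 0.02 to 0.08 over the assumed wear ranges, and the test's conclusion does not change. If the two sources were equally accurate, false findings for the device would run at about 9-29% of trials at 50% capture and about 40-98% at 90% capture with Poisson counts (20-81% overdispersed), against about 5% when matched.

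These figures rest on assumed seizure rates, wear patterns and count distributions, on wear being unrelated to seizures, and on diary errors being omissions only. The point supports neither a claim that a positive primary result would be spurious nor one that diary sensitivity is distorted. It affects the estimate in (C), the diary's false positive rate and positive predictive value, and its Bland-Altman mean difference.

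**What to change.** In Table 1, Outcomes item (B), and sections 4.1 and 4.3:

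1. Define the primary correlation B, and the diary's Bland-Altman analysis, positive predictive value and false positive rate, on diary entries that fall within EEG-recorded time. The recording log needed for objective 6 supplies the intervals.
2. Pre-specify one minimum amount of recording for a month to count, and apply it equally to A and B. The threshold, and the handling of entries with a date but no clock time, are for the trial team to set before analysis.
3. Report the all-entries version as a sensitivity analysis, which keeps the real-world, whole-period view.

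If the full protocol or SAP already matches entries to recorded time, one clause in each of these places is enough.

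The cost is wording and a merge of two data sets already being collected, with no new visits or participants. There are two downsides: some diary entries go unused in the primary analysis, and any excluded month shortens a Spearman series that has only six points.

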### Statistical analysis of primary outcome measures

4.1

The research team will review raw EEG data from 24/7 EEG SubQ to identify seizures as the ‘ground truth’. We will assess the improvement in accuracy of seizure documentation using AI‐driven algorithm with rapid expert review applied to 24/7 EEG SubQ data (‘24/7 EEG SubQ detected seizures’), compared to using self‐reported participant diary alone. We will estimate for each participant the Spearman correlation between monthly diary report and ground‐truth, and the Spearman correlation between monthly 24/7 EEG SubQ detected seizures and ground truth. We will test the hypothesis that, across the cohort, the correlation between 24/7 EEG SubQ detected seizures and ground truth is higher than between the diary and ground truth. We will also calculate for diary and 24/7 EEG SubQ detected seizures the sensitivity, specificity, false positive rate, positive predictive value, and negative predictive value, for seizure detection. We will report using Standards for the Reporting of Diagnostic accuracy studies (STARD) principles.^31^

Feasibility and acceptability will be assessed by the proportion of participants who continue in the study for >3 months of 24/7 EEG SubQ data collection.

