## STUDY PROCEDURES

3

During Visit 1, participants will complete baseline patient reported outcome measures (PROMs) and subsequently will undergo an online qualitative interview at baseline. Following this, they will be implanted with the 24/7 EEG SubQ by the local surgical team (Visit 2). The implant is inserted under local anesthesia in the pre‐auricular region in the subgaleal space on a predetermined side (i.e. right or left) and orientation based on the treating clinician's instruction. The electrodes can be positioned anywhere in the arc illustrated on the right of Figure 1 panel C, which allows a wide range of focal epilepsies to be included. We aim to position the electrodes where ictal EEG changes are likely to be detected based on previous electroclinical data. Any surgical specialty with expertise operating within the head and neck region is eligible to implant the 24/7 EEG SubQ. The participant is discharged after a two‐hour observation period with an implant ID card. Visit 3 occurs 10–14 days after implantation, when procedures for data collection will again be explained, and the participant will commence EEG data collection and begin keeping an electronic seizure diary (Helpilepsy; Neuroventis, Overijse, Belgium).^27^ During 6 months of data collection, participants will receive a minimum of monthly feedback regarding recorded EEG data from their treating clinician. They will repeat PROMs at 2 months (Visit 4) and 6 months (Visit 5) and an online qualitative interview prior to explantation after data collection is complete. The participant will then exit the study. Treating clinicians will complete standardized questionnaires assessing their experience using the 24/7 EEG SubQ during the study and after the participant's last visit. A treating clinician at each site will participate in a qualitative interview after the last participant at that site has had his/her final visit.

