### Data collection

3.1

PROMs will be collected at Visits 1 (baseline), 4 (2 months), and 5 (6 months) via the electronic data capture system REDCap (see Table 1 for details).^28^ Use of REDCap forced responses to progress surveys and email prompts to review data will be utilized to ensure data completeness with both participants and investigators.

**TABLE 1 epi470064-tbl-0001:** Primary and secondary objectives with corresponding outcome measures.

Primary objective	Corresponding endpoint(s)/outcome variable(s)
To investigate the diagnostic accuracy of 24/7 EEG™ SubQ Solution	Within‐participant correlation between seizure counts per month estimated from rapid clinician review of annotated 24/7 EEG™ SubQ data and ‘ground truth’ EEG seizure occurrences per month (derived from expert research team review of 24/7 EEG™ SubQ EEG data), across the 6 months of the study (‘correlation A’). Within‐participant correlation between seizure counts per month from participant‐reported seizure diary and ‘ground truth’ EEG seizure occurrences per month (derived from expert research team review of 24/7 EEG™ SubQ EEG data), across the 6 months of the study (‘correlation B’). Average difference between ‘correlation A’ and ‘correlation B’, across participants. Average difference between the number of AI‐driven automated seizure detections produced by EpiSight software and seizure counts estimated from rapid clinician review of annotated 24/7 EEG™ SubQ data, across participants. Clinician rating on the question ‘Overall, after review of annotated 24/7 EEG™ SubQ data for all participants, how would you rate your rapid clinician review?’, i.e., average score on a 10‐point Likert scale (‘the AI‐driven algorithm is very accurate compared to my rapid review’ (10) to ‘the AI‐driven algorithm is very inaccurate compared to my rapid review’ (1))

Secondary objectives	Corresponding endpoint(s)/outcome variable(s)
2 To investigate the clinical relevance of 24/7 EEG™ SubQ Solution	Change over time for average HCP questionnaires ‘Communication’, ‘Insight’ & ‘Potential of 24/7 EEG™’ scores at baseline, 2 months and 6 months

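### Correlation A compares two readings of one SubQ recording, so A minus B favours the device and cannot show accuracy for all true seizures

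*Protocol article*

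**What the plan says.** **Reference.** Section 4.1 states "The research team will review raw EEG data from 24/7 EEG SubQ to identify seizures as the" ground truth. Section 4 repeats that it is "derived from expert research team review of 24/7 EEG SubQ data".

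**Index test.** In section 4, correlation A uses monthly counts "estimated from clinician review of annotated 24/7 EEG SubQ data". Section 3.2 describes the steps before that review: an AI detector, then technicians who remove suspected false positives. Correlation B sets the diary against the same reference.

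**Coverage.** Section 3 places the implant on one predetermined side. Section 3.1 records two channels.

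**Claim.** The primary objective in Table 1 reads "To investigate the diagnostic accuracy of 24/7 EEG™ SubQ Solution". Section 4.1 adds sensitivity, specificity and predictive values for diary and device, reported on STARD principles.

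**Planning.** Section 2.4 takes a mean diary correlation of 0.30 (SD 0.41) from a study whose reference was an intracranial device, chooses 0.5 as target, and says "We seek to demonstrate a higher correlation between 24/7 EEG SubQ and the ground truth seizure occurrences". It gives 85% power with 33 participants at alpha 0.05.

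No reference independent of SubQ is named, and the limitations in section 6 do not mention the shared recording.

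**The concern.** In a diagnostic accuracy study the reference should be able to reveal what the index test misses. Here it cannot reveal what the implant misses, because it is read from the implant. It can reveal only what the AI, technician and rapid-review steps miss or add within that signal.

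The diary is treated differently. A participant may correctly record a seizure that two channels on one side do not show. That entry has no counterpart in the reference, so it disturbs the match between diary and reference counts and lowers B. In the sensitivity and predictive-value analysis it becomes a diary false positive.

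The risk is a conclusion that SubQ documents seizures more accurately than a diary when the data support only a statement about SubQ-visible seizures.

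**Working it through.** **1. The plan's own figure.** Difference 0.5 - 0.3 = 0.2. Standardised by 0.41: 0.2 / 0.41 = 0.488. With n = 33 and one-sided alpha 0.05, a paired t test gives 86.4%. A Wilcoxon signed-rank test (relative efficiency 3/pi) gives 84.9%, which matches the stated 85%. Two-sided, the figures are 77.6% and 75.5%. So the 85% reproduces one-sided as arithmetic. Its inputs are the difficulty: 0.30 and 0.41 were measured against an independent intracranial recording, and 0.5 was chosen on that scale.

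**2. Who loses what.** For a seizure not shown by SubQ, or occurring while the device is not worn:

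- reference count: not included;
- index count: not included, so A is unaffected;
- diary count: included if the participant records it, so B falls.

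**3. Size, as an illustration.** None of these inputs comes from the documents. Assume a mean of 4 true seizures a month over 6 months, with monthly rates varying (gamma, coefficient of variation 0.5). The workflow finds 90% of SubQ-visible seizures, the diary reports 50% of all seizures, and false counts are 10% of the mean for each. Let v be the share of true seizures that SubQ shows. Mean Spearman coefficients over 20,000 simulated participants:

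| v | A, SubQ reference | B, SubQ reference | A - B as planned | Device, all true seizures | Diary, all true seizures | Difference, all true seizures |
|---|---|---|---|---|---|---|
| 100% | 0.90 | 0.68 | +0.22 | 0.90 | 0.68 | +0.22 |
| 80% | 0.88 | 0.64 | +0.24 | 0.81 | 0.69 | +0.12 |
| 50% | 0.84 | 0.54 | +0.30 | 0.65 | 0.69 | -0.04 |
| 30% | 0.79 | 0.45 | +0.34 | 0.50 | 0.68 | -0.18 |

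As v falls, the planned difference rises, while the difference against all true seizures falls and changes sign.

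**4. Sensitivity to the inputs.** At v = 50%, the planned difference is +0.41 with no extra variation between months (Poisson) and +0.24 with a coefficient of variation of about 0.7. Against all true seizures it is about -0.04 in both cases. At a mean of 1 a month, v = 50% gives 0.86 - 0.48 = +0.38 as planned against 0.60 - 0.64 = -0.04. At 8 a month it gives 0.86 - 0.63 = +0.23 against 0.71 - 0.74 = -0.03. The direction of the bias is the same throughout; its size is not.

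**The case against.** **The reference is disclosed and the contrast has value.** The article states how the ground truth is derived each time it defines the outcomes, and there it counts EEG seizure occurrences. Whether AI plus technician plus rapid review reproduces full expert reading is a real question, because that chain can miss or add events. This stands: A measures that validly, and B validly measures how the diary tracks SubQ-visible seizures. It does not rescue the broader wording in Table 1, 2.4 and 4.1.

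**The bias may be small.** Section 3 places electrodes where ictal changes are expected from earlier electroclinical data. At 80% visibility the difference is inflated but keeps its sign. This stands too: the documents do not give the visible share.

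**Three stronger readings are tempting but not supported.**

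- *A is close to 1 by construction and rejection is close to certain.* A near 1 would need almost no false positives to survive screening. Section 3.2 reports 5.5 per 24 h before screening, or 5.5 x 30 = 165 a month. If 2 a month survive (2 / 165 = 1.2%, an assumption) and sensitivity is 89%, simulated mean A is 0.43-0.47 at 0.83 seizures a month, 0.58-0.66 at 2 and 0.69-0.80 at 4.
- *The reference readers see the AI and technician marks.* Section 3.2 says "Continuous EEG monitoring will generate substantial data; therefore, an automated solution is required", and investigators get the data through the analysis software. But section 4.1 specifies raw EEG, nothing says that marks are shown during the reference reading, and masking may be set out in the full protocol.
- *Feedback spoils the diary comparison.* Section 3 says "During 6 months of data collection, participants will receive a minimum of monthly feedback regarding recorded EEG data from their treating clinician". That feedback is part of the intervention. Its effect on B has no fixed direction, and a better diary would shrink A minus B.

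**Conclusion.** The point holds in a limited form. Index and reference share one recording, so A minus B is biased towards SubQ by an amount that depends on the unknown share of seizures the implant shows. The contrast can support a claim about agreement with expert reading of the SubQ signal. It cannot support one about accuracy for all true seizures.

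Under the stated assumptions the effect ranges from modest inflation at 80% visibility (+0.24 against about +0.12) to a reversed sign at 50% (about +0.24 to +0.41 against about -0.04). These figures illustrate the mechanism and do not predict the trial's result. The 0.30, 0.41 and 0.5 in section 2.4 belong to a different reference, so the 85% power does not describe the planned contrast.

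This should be corrected before analysis, because it governs what the primary result may be said to show. It does not invalidate the trial, and no new reference procedure is needed if the claim is narrowed.

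**What to change.** 1. **Restate the claim.** In Table 1, 2.4 and 4.1, define A as agreement of the rapid-review workflow with expert reading of the same SubQ recording, and B as agreement of the diary with SubQ-visible seizures. Limit the sensitivity, specificity and predictive-value claims in the same way. Add the shared recording to the limitations, and say in 2.4 that the planning values come from a different reference.
2. **Add a prespecified sensitivity analysis.** Class diary entries made for recorded hours without a SubQ correlate as unconfirmed, not as false positives, and repeat A minus B without them. State that this version favours the diary, since it also removes genuine diary errors. The two analyses then show how far the result depends on how such entries are scored.
3. **Protect the reference reading.** If the full protocol does not already require it, have the research team lock its reading before seeing AI marks, technician annotations, weekly reports or the diary. This cannot be recovered afterwards.

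**Cost.** A narrower claim and somewhat slower reference reading. No extra participants, readers or procedures are needed, since raw review by the research team is already planned.
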